**Methods/design:**

This is a prospective, randomized, controlled clinical trial that aimed to examine the capability of multimodal imaging techniques for the evaluation of CVR to improve treatment of patients with ischemic stroke. A total of 66 eligible patients will be recruited from Renji Hospital, Shanghai Jiaotong University School of Medicine. The patients will be categorized based on CVR into two subgroups as follows: CVR > 10% group and CVR < 10% group. The patients will be randomly assigned to medical management, percutaneous transluminal angioplasty and stenting, and intracranial and extra-cranial bypass groups in a 1:1:1 ratio. The primary endpoint is all adverse events and ipsilateral stroke recurrence at 6, 12, and 24 months after management. The secondary outcomes include the CVR, the National Institute of Health stroke scale and the Modified Rankin Scale at 6, 12, and 24 months.

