## Methods/design

### Study design

This prospective, randomized, controlled clinical trial aimed to examine the efficacy of multimodal image data based on CVR to treat ischemic stroke. A total of 66 patients, who met the inclusion criteria, were admitted to Center for Reproductive Medicine at Renji Hospital, Shanghai Jiaotong University School of Medicine (Shanghai, China). The eligible patients were categorized based on CVR into two groups as follows: CVR > 10% group and CVR < 10% group. In addition, these two groups were randomly assigned to the groups of medical management, single angioplasty, PTAS, and IC-EC bypass in a 1:1:1 ratio. Fig. 1 shows the study flowchart of our trials.

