### Sample size and data analysis

The number of patients included in the registry was equal to 60, and this trial involved 66 eligible ischemic-stroke patients, in which about 10% of patients were lost to follow-up. Data were presented as mean ± standard deviation (SD) for continuous variables, and as frequency for categorical variables. Significances between variables were analyzed using the chi-square test. Associations between clinical variables and outcomes were analyzed, and predictors of long-term outcome were identified using univariate and multivariate regression analyses. The difference was expressed as an odds ratio (OR, with 95% confidence interval (CI)), and *P* < 0.05 was considered statistically significant.

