## Discussion

Previous studies have shown that medical management, PTAS, and IC-EC bypass can be applied to ischemic-stroke patients; however, which treatment method is more beneficial has remained elusive [4, 15]. The present trial was designed to indicate whether measurement of CVR using multimodal imaging is helpful to improve the treatment strategy for adult patients with intracranial arterial stenosis or occlusion.

Increased risk of stroke was found to be associated with hemodynamic failure, which can be assessed with measurement of CBF using (^15^O-)H_2_O PET [16]. This gold-standard technique, however, has not been presented for routine clinical imaging. Standardized blood oxygen-level-dependent functional MRI + CO_2_ is a noninvasive and potentially widely applicable method to assess whole-brain quantitative CVR. In addition, SPECT/CTP combined with CO_2_ challenge enables scholars to measure CBF and CVR, representing the degree of hemodynamic failure [17, 18].

It has been previously demonstrated that there is an association between CVR impairment and risk of stroke conserved across testing modality (TCD or nuclear medicine (NM) technique) as well as the nature of the vasodilatory stimulus (acetazolamide or variation in inspired CO_2_ levels). TCD is relatively inexpensive and widely available, while it does not provide additional information about brain parenchyma and is technically impossible in some cases due to lack of acoustic windows. In the present study, we accurately evaluated CVR for ischemic-stroke patients by multimodal imaging methods (MRI, CT, or SPECT), and explored the recurrence of ischemic stroke after treatment; thus, we can develop a new method for accurate diagnosis and treatment of ischemic stroke [9, 19, 20]. Our approach possesses a number of novel features compared with other relevant trials. Firstly, CVR in the ischemic-stroke patients was evaluated by multimodal imagine methods because those are widely applicable to assess whole-brain quantitative CVR. Some researchers have reported that SPECT is more sensitive than PET in the evaluation of CBF and cerebral perfusion, while its spatial resolution is negligible [21, 22]. The above-mentioned findings demonstrate that multimodal imaging techniques can accurately reflect changes in CVR. Secondly, the current study categorized the eligible patients into the groups of medical management, PTAS, and IC-EC bypass based on and the rates of CVR.

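### The objective is whether CVR should guide treatment, but the stated analysis names no arm comparison, CVR grouping or arm-by-CVR term, and the design can at most explore whether treatment effects differ by CVR group

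*Protocol article*

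**What the plan says.** **Objective.** The Study design section says the trial "aimed to examine the efficacy of multimodal image data based on CVR to treat ischemic stroke". The Discussion says: "The present trial was designed to indicate whether measurement of CVR using multimodal imaging is helpful to improve the treatment strategy". The Abstract and the Introduction put the aim in similar terms.

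**Grouping and allocation.** Under Study design: "The eligible patients were categorized based on CVR into two groups as follows: CVR > 10% group and CVR < 10% group". The next sentence reads: "In addition, these two groups were randomly assigned to the groups of medical management, single angioplasty, PTAS, and IC-EC bypass in a 1:1:1 ratio". That names four treatments under a three-part ratio, whereas the Abstract has three arms (medical management plus "percutaneous transluminal angioplasty and stenting, and intracranial and extra-cranial bypass groups in a 1:1:1 ratio"). The Discussion describes assignment differently: "the current study categorized the eligible patients into the groups of medical management, PTAS, and IC-EC bypass based on" CVR.

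**Analysis.** The Sample size and data analysis section gives descriptive summaries and a chi-square test between variables that it does not name. It continues: "Associations between clinical variables and outcomes were analyzed, and predictors of long-term outcome were identified using univariate and multivariate regression analyses". Differences are to be given as odds ratios with 95% confidence intervals at P < 0.05. The section does not say which groups the difference is between.

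**CVR measurement.** According to Study endpoints, CVR is measured at enrolment and at 6 months, 1 year and 2 years. It is also listed among the functional outcomes.

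**The concern.** Saying that CVR should guide treatment is a claim about effect modification: the better treatment, or the size of its advantage, depends on CVR. The Introduction makes the same kind of claim when it justifies the 10% cut, citing an earlier bypass study to say that bypass is unlikely to benefit patients above it. To support such a claim one needs the difference between arms within each CVR group, and a measure of how much those differences diverge.

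The stated analysis looks for predictors of outcome. If CVR were among them, its odds ratio would show that patients with low CVR fare worse or better overall. The Discussion already treats an association between impaired CVR and stroke risk as established, so that result would add little. The danger is that a significant CVR predictor would be reported as evidence that CVR-guided treatment works. CVR is also a follow-up outcome, and the analysis section does not separate baseline from later values. A later value is affected by treatment and cannot serve as the guiding variable.

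**Working it through.** **1. What the design can contrast.** All eligible patients have CVR measured (Treatment protocol), and both CVR groups are then allocated to the treatments (Study design). No arm is managed without knowledge of CVR, so there is no randomised comparison of imaging-guided with unguided care. Two questions remain: how the treatments compare, and whether that comparison differs between the CVR groups.

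**2. What the stated analysis delivers.**

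| Question | Needed | Named in the analysis section |
|---|---|---|
| Which treatment is better? | Arm comparison | No; the chi-square variables are not named |
| Does the effect differ by CVR? | Arm effect within each CVR group; arm-by-CVR term | No |
| Is CVR prognostic? | CVR main effect | Possible, if CVR counts as a clinical variable |
| Does imaging-guided care help? | An arm managed without CVR | Not available in this design |

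**3. The plan's own figure.** 60 × 1.10 = 66, which matches the stated enrolment (60/0.90 would give 67). The base of 60 comes with no effect size, event rate or power, so it cannot be checked further.

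**4. Patients per cell.** 60 evaluable patients / (3 arms × 2 CVR groups) = 10. This assumes three arms and an equal CVR split; the article does not state the split. At 30:70 the cells hold 6 and 14 patients, and at 20:80 they hold 4 and 16.

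**5. Precision of a pairwise interaction odds ratio.** For two arms and two CVR groups with common risk p:

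SE(log OR) = √[(2/n₁ + 2/n₂) / (p(1−p))], and the 95% interval is the estimate divided and multiplied by exp(1.96 × SE).

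The article gives no risk for its own endpoint, so p is assumed. The range runs from 15% (the medical-arm figure in the stenting trial cited in the Introduction) to 50%.

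- n₁ = n₂ = 10, p = 0.15: SE = √(0.4/0.1275) = 1.77; factor exp(3.47) ≈ 32
- n₁ = n₂ = 10, p = 0.23: SE = √(0.4/0.1771) = 1.50; factor ≈ 19
- n₁ = n₂ = 10, p = 0.50: SE = √(0.4/0.25) = 1.26; factor exp(2.48) ≈ 12
- 30:70 split: factor ≈ 15 (p = 0.50) to 44 (p = 0.15)
- 20:80 split: factor ≈ 22 (p = 0.50) to 77 (p = 0.15)

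At p = 0.15 a cell of 10 expects 1.5 events, so the large-sample formula is only a guide to the order of magnitude.

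**6. Power for the interaction on the risk-difference scale** (two-sided 0.05, normal approximation, 60 evaluable, assumed risks):

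| Low CVR, A v B | High CVR, A v B | 50:50 | 30:70 | 20:80 |
|---|---|---|---|---|
| 30% v 10% | 15% v 15% | 13% | 12% | 10% |
| 40% v 10% | 15% v 15% | 24% | 20% | 16% |
| 50% v 10% | 10% v 10% | 42% | 33% | 25% |
| 50% v 10% | 10% v 30% | 66% | 57% | 46% |

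At a 50:50 split, 80% power would need 654, 312, 156 and 84 evaluable patients in the four scenarios.

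**The case against.** **This is an article, and a statistical analysis plan may exist.** Model terms and subgroup tests are often left to it, and the regression as described does not exclude arm, CVR group or their interaction. That is fair, and it limits the point to what the article names. But the article does state a purpose for its regression, finding predictors of outcome, and that purpose does not match the objective. A separate plan could add terms, yet the published objective would still ask for a contrast that the design lacks.

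**A reader might infer that the plan pools patients and ignores CVR.** The text does not say so. The chi-square variables are not named, and no pooling is described.

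**A reader might infer that the arm comparison has a wrong standard error.** This would need randomisation stratified by CVR, which is not clearly stated: the randomisation section does not mention it, and the Discussion conflicts with it. Even then the effect is small and conservative. With assumed group risks of 10% and 30% in equal groups, the mean within-group variance is (0.09 + 0.21)/2 = 0.15, against 0.20 × 0.80 = 0.16 unadjusted. The ratio of standard errors is √(0.15/0.16) = 0.97, so ignoring the groups makes the standard error about 3% too large.

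**The design answers other questions.** It does. The Discussion also asks which treatment is more beneficial, and the Introduction wants the change in CVR after treatment. Arm comparisons address both without an interaction.

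**The interaction would be hopelessly imprecise.** This stands. It rules out the interaction as the main confirmatory model, but it does not justify leaving the objective as written.

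**Conclusion.** The point holds in a limited form. The objective concerns CVR-guided treatment. The stated analysis names no arm comparison, no CVR grouping and no arm-by-CVR term, and a CVR main effect would show prognosis only. The design offers no randomised test of imaging itself.

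It would go too far to say that the data cannot address CVR at all. If treatment is randomised within CVR groups, they can support an exploratory look at effect modification. If treatment is instead chosen from CVR, as the Discussion can be read, treatment and CVR are confounded and that look is lost. The two accounts must be reconciled before anything else.

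The precision figures in the working rest on three arms, 60 evaluable patients and assumed risks and CVR splits. The 15% and 23% risks come from a cited trial with a different endpoint. This trial's endpoint includes all adverse events and may be more frequent, which is why the range extends to 50%. Under all these assumptions the interaction is very imprecise and can only generate hypotheses.

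A minor related point is that the two CVR groups leave a value of exactly 10% unassigned. How many patients this affects depends on rounding that the article does not give.

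**What to change.** 1. Reconcile the Study design section with the Discussion on how treatment is allocated, and with the Abstract on the number of arms. State whether randomisation takes place within CVR groups.
2. Restate the objective as the comparison of treatments, with the exploratory aim of asking whether the treatment effect differs by baseline CVR group.
3. Replace the predictor search with an arm comparison adjusted for baseline CVR group. Report arm differences with 95% confidence intervals within each CVR group.
4. Add an arm-by-baseline-CVR-group interaction, fitted by penalised logistic regression because events per cell will be few, and label it hypothesis-generating.
5. State that neither a CVR main effect nor this design can show that imaging-guided treatment improves outcome.
6. Assign a CVR of exactly 10% to one group.

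The cost is wording and a more modest conclusion. CVR is already scheduled at enrolment, so no new measurement is needed. The downside is that the interaction interval will be very wide. If the sponsor wants a confirmatory answer on CVR, the sample size has to be derived for the interaction instead.

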## Introduction

Stroke is the second most common cause of death and the major cause of disability worldwide after ischemic heart disease, especially in developing countries [1]. Ischemic stroke occurs when a blood vessel supplying blood to a part of the brain is obstructed, and it accounts for about 87% of all strokes. A remarkable risk of recurrent ischemic stroke was reported in patients with symptomatic, major cerebral arterial occlusion or stenosis [2]. Therefore, an effective therapeutic approach for intracranial arterial stenosis is urgently required.

The treatment of ischemic stroke has been investigated by a number of high-quality trials: The Japanese extracranial-intracranial bypass (EC-IC) bypass trial (JET2) study revealed that compared with the medical arm of the Japanese EC-IC bypass trial (JET) study including patients with cerebral blood flow (CBF) < 80% and cerebrovascular reactivity (CVR) < 10% as a historical control, the incidence of ipsilateral stroke recurrence was significantly lower in the JET2 study, demonstrating that EC-IC bypass surgery is unlikely to benefit patients with CBF > 80% or CVR > 10% [3]. Another recent trial involving aggressive medical treatment with or without stenting in high-risk patients with intracranial arterial stenosis (SAMMPRIS), demonstrated the use of aggressive medical management rather than percutaneous transluminal angioplasty and stenting (PTAS) with the Wingspan system in high-risk patients with atherosclerotic intracranial arterial stenosis [4]. AL Hasan conducted a trial for treating ischemic stroke, and showed a 14.7% risk of stroke or death in the stenting group versus 5.8% in the medical group at 30 days, and 23% in the stenting group versus 15% in the medical group at a median follow-up of 32.4 months. However, the treatment strategy of intracranial arterial stenosis or occlusion mainly depends on the degree of vascular stenosis, with or without consideration of hemodynamic factors at the distal end-to-side anastomosis of a bypass graft and CVR factors, or steady-state vascular parameters, such as CBF and cerebral blood volume (CBV). Hence, we present a study protocol for the measurement of CVR using multimodal imaging data for cerebral arterial occlusion or stenosis patients.

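### The odds ratio is the only effect measure named, but with about 20 patients per arm it can be 0 or infinite for ipsilateral stroke, with no finite confidence interval

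*Protocol article*

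**What the plan says.** Under Sample size and data analysis, the protocol article sets the test ("Significances between variables were analyzed using the chi-square test"), the threshold (P "< 0.05 was considered statistically significant") and the effect measure: "The difference was expressed as an odds ratio (OR, with 95% confidence interval (CI". It also plans univariate and multivariate regression. It names no risk difference or risk ratio, and no exact or penalised method.

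The same section gives the base size: "The number of patients included in the registry was equal to 60". Enrolment is set at 66 to allow for dropout of about 10%. The Abstract gives the allocation: "medical management, percutaneous transluminal angioplasty and stenting, and intracranial and extra-cranial bypass groups in a 1:1:1 ratio". Patients are also divided into two CVR groups at 10%.

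On endpoints the Abstract says: "The primary endpoint is all adverse events and ipsilateral stroke recurrence at 6, 12, and 24 months after management". The Study endpoints section instead makes adverse events primary and ipsilateral stroke secondary. Stroke recurrence is a binary outcome under either reading.

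The article states no expected event rate for this trial. The Introduction cites an earlier trial that "showed a 14.7% risk of stroke or death in the stenting group versus 5.8% in the medical group at 30 days". The longer-term figures it gives for that trial, at a median of 32.4 months, are 15% (medical) v 23% (stenting).

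**The concern.** An odds ratio divides one arm's odds by the other's. If an arm has no event, its odds are 0, so the ratio is 0 or infinite (0/0 if both arms have none) and the usual log-scale interval does not exist. A logistic model on the same data, which reporting an odds ratio implies, fails by separation.

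With about 20 patients per arm and a possibly infrequent outcome such as ipsilateral stroke, an empty arm is a realistic result. It also tends to coincide with a significant test, because at this size a significant difference in a rare outcome often means several events against none. The report could then give a P value without a usable estimate of the size of the difference. An improvised 0.5 correction could even seem to contradict the test.

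**Working it through.** **1. Patients per arm.** The plan's own figure first: 60 × 1.10 = 66, as stated. (Dividing instead gives 60/0.9 = 66.7, so 67; and 66 × 0.9 = 59.4.) The base of 60 cannot be reproduced, since no effect size, event rate or power is given. Evaluable per arm: 60/3 = 20. Within a CVR group, assuming an even split: 20/2 = 10.

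**2. Chance of a zero cell in one pairwise comparison.** With risks p1 and p2 and n per arm, ignoring the negligible chance that every patient in an arm has an event:

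P(zero cell) = 1 − [1 − (1 − p1)^n] × [1 − (1 − p2)^n]

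The risks are the two stroke-or-death pairs in the Introduction, used as illustrations.

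- 5.8% v 14.7%, n = 20: 0.942^20 = 0.303 and 0.853^20 = 0.042; 1 − 0.697 × 0.958 = 0.33.
- 15% v 23%, n = 20: 0.85^20 = 0.0388 and 0.77^20 = 0.0054; 1 − 0.9612 × 0.9946 = 0.044.
- 5.8% v 14.7%, n = 10: 0.550 and 0.204; 1 − 0.450 × 0.796 = 0.64.
- 15% v 23%, n = 10: 0.197 and 0.073; 1 − 0.803 × 0.927 = 0.26.

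**3. Relation to the test.** All 2×2 tables were enumerated with exact binomial weights and an uncorrected Pearson chi-square at P < 0.05.

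| Risks | n per arm | Zero cell | Significant | Both | Zero cell if significant | Zero cell if not |
|---|---|---|---|---|---|---|
| 15% v 23% | 20 | 4.4% | 9.7% | 2.9% | 30% | 1.6% |
| 5.8% v 14.7% | 20 | 33% | 12.8% | 10.3% | 81% | 26% |
| 15% v 23% | 10 | 26% | 4.4% | 3.9% | 88% | 23% |
| 5.8% v 14.7% | 10 | 64% | 2.7% | 2.6% | 98% | 63% |

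The conditional figures follow from the others, for example 10.3/12.8 = 0.81 and 2.9/9.7 = 0.30. At 20 v 20 the smallest significant tables are 0 v 4, 1 v 6 and 2 v 8 events.

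**4. Three arms.** With equal risk p in three arms of 20, the chance that at least one arm has no event is 1 − [1 − (1 − p)^20]^3: 74% at p = 5%, 32% at 10% and 11% at 15% (assumed risks).

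**5. One worked table, 5/20 v 0/20.**

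- Chi-square = 40 × (5 × 20 − 0 × 15)² / (20 × 20 × 5 × 35) = 5.71, P = 0.017.
- The odds ratio is infinite.
- With 0.5 added to each cell: (5.5 × 20.5)/(15.5 × 0.5) = 14.5. The log standard error is √(1/5.5 + 1/15.5 + 1/0.5 + 1/20.5) = 1.515, so the 95% interval is 0.75 to 283. It includes 1 although the test is significant.
- Risk difference: 25 points. The Wilson limits are 11.2% to 46.9% for 5/20 and 0% to 16.1% for 0/20. Newcombe's limits are 25 − √(13.8² + 16.1²) = 3.8 and 25 + √(21.9² + 0²) = 46.9 points. The interval is finite and agrees with the test.

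**6. Sensitivity.** With 22 per arm (no loss to follow-up), a zero cell occurs in 3.1% (15% v 23%) and 29% (5.8% v 14.7%) of trials. With Yates' correction at 20 per arm, 29% and 71% of significant results have one. For common outcomes (assumed risks) at 20 per arm, it is 0.1% at 30% v 60% and about 1% at 50% v 80%. At 10 per arm the latter rises to 11%.

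**The case against.** Five objections deserve weight.

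- **Scope of the sentence.** A reader might infer that every arm difference must be an odds ratio. The text refers only to the difference, names no comparison or endpoint, and directly follows the regression sentence, where odds ratios are natural. That stronger reading is not supported. What stands is that no other effect measure is named for a binary outcome.
- **Handling of zero cells belongs in an SAP.** Largely true. The article fixes no Wald interval and no 0.5 correction, and an exact conditional interval fits its wording. For 5/20 v 0/20 that interval runs from 1.02 to infinity: it agrees with the test but has no upper limit. So the sentence need not leave the report empty-handed, but the measure it names remains a poor fit for sparse data.
- **Time horizon.** The 33% and 81% use 30-day risks, while the endpoints fall at 6, 12 and 24 months. The longer-term pair gives only 4.4% at 20 per arm. This stands, and rules out saying without qualification that the odds ratio will often be undefined. In the other direction, the cited risks are for stroke or death, and ipsilateral stroke alone may be rarer.
- **Denominators.** A reader might take the 81% or 98% to mean that the trial will probably yield a significant result without an estimate. It will not: the joint event occurs in 10.3% and 2.6% of trials respectively. At 15% v 23% with 20 per arm, 70% of significant results have a finite odds ratio.
- **CVR groups and adverse events.** The 10-per-arm figures assume an even split and arm contrasts within CVR groups, and the analysis section states neither. Adverse events of any kind may be common, and then whole-arm odds ratios are nearly always finite. An odds ratio that exceeds the risk ratio for a common event is not an error.

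**Conclusion.** The point holds in a limited form. The one effect measure the protocol names is poorly suited to ipsilateral stroke at this size. In whole arms of 20, a pairwise odds ratio has no finite value or interval in about 4% to 33% of trials across the two cited pairs of risks; with 10 per arm the range is 26% to 64%. The problem is concentrated among significant results, where an effect size is most wanted, but the combination of significance and a zero cell arises in only about 3% to 10% of trials.

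This rests on borrowed stroke-or-death risks, independent binomial outcomes, three equal arms and, for the smaller groups, an even CVR split. The documents do not support saying that the odds ratio will usually be undefined, or that the trial could not report a treatment difference. Nor does a better effect measure cure the small sample: at 20 per arm the normal-approximation power is only about 9% (15% v 23%) to 15% (5.8% v 14.7%). The change is worth making because it is cheap and the replacement stays defined with no events.

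**What to change.** Replace the effect-measure sentence with wording such as: *Arm differences in ipsilateral stroke and in adverse events will be expressed as risk differences with 95% score-based confidence intervals (Newcombe or Miettinen-Nurminen), which remain defined when an arm has no events. Where an odds ratio is reported or a logistic model is fitted, Firth penalised likelihood with profile-likelihood intervals will be used.*

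Name one of the two score methods in advance, since they can differ at the margin. For 4/20 v 0/20 the chi-square is 4.44 (P = 0.035). Newcombe's lower limit is 20 − √(11.9² + 16.1²), just below 0. The Miettinen-Nurminen statistic at zero difference is 4.44 × 39/40 = 4.33, above 3.84, so that interval excludes 0 and agrees with the test.

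The chi-square test can stay. Its exact size for three arms of 20 is 3.3%, 3.9%, 4.5% and 5.2% at common risks of 5%, 10%, 15% and 23%.

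The cost is analysis wording and code, with no change to recruitment, data collection or patient care. The one downside is that Firth estimates are shrunk slightly towards no effect.
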